**Figure 1 F1:**
[figure not shown]
**Study design and subject allocation**.

##### Data collection

Table 4 summarizes the parameters and outcomes of interest. Data that will be collected include patient demographics (age, gender, race, length of hospital stay, duration of delirium(days); comorbidity and severity of illness data using modified Charlson's comorbidity index [43] and modified severity of Illness index [44]. Cognitive status will be assessed by way of the locally validated cognitive screening instrument (Abbreviated Mental Status Test (AMT)) [37] and functional status (using modified Barthel Index) [45] during the initial and pre-discharge phase of patient's admission. This was administered by a single trained assessor. We also aim to look at the rate and duration of physical restraint and frequency of chemical restraint use. To adjust for the differences antipsychotic usage, we will use chlorpromazine equivalence [46] to look at the total antipsychotic usage during the admission, as well as frequency of antidepressant and benzodiazepine use. Rate of falls and physical injuries, urinary catheter usage, complications of immobility (pressure ulcer) and rate of nosocomial infections will be systematically collected during patient's hospital stay. The functional outcomes in the geriatric patients with delirium include follow-up phone interview at baseline, 6 months and 12 months later. Hospitalisation, morbidity and mortality data over the same follow-up period will also be collected during those time intervals. These data will be obtained from patients in the GMU patients and usual care (control group). We will assess family/caregiver satisfaction via surveys conducted for loved ones of delirious patients in GMU versus those whom are receiving usual care.

**Table 4 T4:** Overview of assessments used in GMU implementation study

Domain	Type of assessment/Outcomes			
		Pre-GMU implementation	GMU implementation	GMU concurrent controls
**Baseline demographics**	**Age, race, gender, length of hospital stay**	X	X	X
**Cognition**	**AMT** **CMMSE**	X -	X X	X X
**Comorbidity**	**Charlson's index** **SIRS**	X X	X X	X X
**Delirium severity**	**CAM severity score** **DRS-98**	- -	X X	X X
**Functional status**	**Modified BI**	X	X	X
**Physical restraints**	**Daily records**	X	X	X
**Medications**	**Antipsychotics (chlorpromazine equivalence)** **Antidepressants** **Benzodiazepines**	X	X	X
**Morbidity and mortality**	**Rate of falls** **Physical injuries** **Urinary catheter usage** **Pressure ulcer development** **Rate of nosocomial infections** **Inpatient mortality**	X	X	X
**Qualitative measures**	**Family satisfaction survey** **Staff satisfaction survey** **Staff knowledge survey**	-	X	X
**Follow-up data (6, 12-monthly)**	**Rate of hospitalization** **Functional status (BI)** **Institutionalisation** **Mortality**	-	X	X

The primary outcome measures we will look at include: (i) Clinical data with regards to duration and severity of delirium; frequency of use of physical restraints, use of pharmacological agents/sedative hypnotics, physical injuries or monthly falls rates; and nosocomial infection rates (ii) Functional outcomes by way of modified Barthel Index score and (iii) Patient/family satisfaction score; all adjusted for baseline demographics and comorbidities. We aim to look at the outcomes measures of patients with delirium admitted to GMU versus those managed under usual care (control group)(refer to Figure 1).

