##### Inclusion, exclusion criteria and patient transfers

The admission criteria for GMU included patients above age of 65 years old assessed to have delirium (either on admission or incident delirium during hospital stay) who were admitted to the geriatric medicine department. Patients were excluded if they had medical illnesses which require special monitoring (e.g. telemetry for arrhythmias or acute myocardial infarction); were deemed to be dangerously ill, in coma or had terminal illness; uncommunicative patients or patients with severe aphasia; severely combative behaviour with high risk of harm; and patients with mania or other severe eye disorders and other contraindications to bright light therapy (such as patients on photosensitising medications). Finally we also excluded patients with respiratory or contact precautions, or there was verbal refusal of GMU stay by family/patient/physician-in-charge.

The GMU will have a dynamic system for transfers (akin to an intensive care unit) whereby patient flow is effected once they are assessed to have met entry or discharge criteria. This will be based upon both subjective and objective approach when the medical team deems the patients to have easy to manage behaviour/minimal or stable behavioural medications and objectively supported by decreased severity of delirium, based on DRS and CAM-severity scores.

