##### Study design and patients recruitment

Our study consist of a pre/post GMU implementation as well as concurrent GMU patients versus patients with delirium managed in the geriatric ward as controls. We will collect available data for patients with delirium admitted to the geriatric department one month prior to GMU implementation. We will give a one-month run-in period after establishment of GMU to smoothen out the initial teething issues and operational issues. The study recruitment commenced in November 2011. We will subsequently identify patients with delirium who meet the inclusion and exclusion criteria for GMU. Using Zelen's method of randomization [41,42], we will admit the patients to GMU and assign others to the control group (see Figure 1). The geriatric team managing the patients in both groups will speak with family regarding the study and if agreeable, consent with be obtained by the GMU co-ordinator and/or geriatric team.

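### In-hospital events and antipsychotic dose are taken over the whole stay rather than from allocation, which dilutes ratios, proportions and risk differences and adds noise to mean differences

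*Protocol article*

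**What the plan says.** All references are to the Protocol article.

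- **Who is eligible.** The section on inclusion, exclusion and transfers accepts delirium "either on admission or incident delirium during hospital stay".
- **When allocation happens.** Under Study design and patients recruitment, identification comes first: "We will subsequently identify patients with delirium who meet the inclusion and exclusion criteria for GMU". Allocation follows: "Using Zelen's method of randomization [41,42], we will admit the patients to GMU and assign others to the control group".
- **Windows stated under Data collection.** For antipsychotics, the aim is to "look at the total antipsychotic usage during the admission". Falls, injuries and catheter use share a sentence with the items in "complications of immobility (pressure ulcer) and rate of nosocomial infections will be systematically collected during patient's hospital stay".
- **No window stated.** For restraints the text says only "We also aim to look at the rate and duration of physical restraint and frequency of chemical restraint use"; Table 4 lists daily records. Delirium duration has no stated start either.
- **Status of these outcomes.** The primary outcome list includes restraints, drug use and "physical injuries or monthly falls rates; and nosocomial infection rates". Catheter use and pressure ulcers appear in the primary aim at the end of the Background.
- **Adjustment.** Outcomes are "all adjusted for baseline demographics and comorbidities". No event or exposure before allocation is named.

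**The concern.** The stated windows open at admission, while the randomised comparison starts later. For a patient whose delirium begins during the stay, the gap may be several days. A fall, a catheter or an antipsychotic dose in that gap cannot have been changed by GMU, and some of these may be part of what led to the delirium being recognised.

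Randomisation makes such events equal in expectation in the two arms, so they do not favour either arm. They do add the same amount to both sides of a ratio or proportion, which moves the contrast towards no effect, and they add variance to everything. With about 50 patients per arm and a sample size set on the Barthel Index alone, these outcomes have no planned margin to absorb the loss.

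The comparison with the pre-implementation cohort is not randomised. There, exposure before delirium need not be equal even in expectation, so whole-stay counting could bias the result in either direction.

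**Working it through.** **1. The plan's own figure.** The sample size is not in question here. A 10-point Barthel difference with SD 14, two-sided 5% (sidedness is not stated) and 90% power needs 42 per group by the normal formula and 43 by the t-test, close to the stated 45. Then 45/0.9 = 50. The counting window does not enter this calculation.

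**2. Rates: inputs.**
- Mean stay with delirium: 15 days (Background).
- Delirium on admission 11-24%, a further 5-35% during the stay (Background; general literature, not this department's case mix). Pairing opposite ends gives the widest incident share s: 5/(24+5) = 0.17 to 35/(11+35) = 0.76.
- Assumed, because the article does not give them: incident cases are allocated on day 3 to 7, and cases present on admission after 0.5 to 2 days.

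**3. Rates: formulas.** The share of patient-days before allocation is f = [s × onset day + (1 − s) × lag]/15. With equal event rates before allocation and in usual care afterwards, and the same stay in both arms, the whole-stay ratio is f + (1 − f) × RR.

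**4. Rates: results for a true RR of 0.50.**

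| s | Onset day | Lag (days) | f | Whole-stay ratio |
|---|---|---|---|---|
| 0.17 | 3 | 0.5 | 0.06 | 0.53 |
| 0.17 | 5 | 1 | 0.11 | 0.56 |
| 0.76 | 5 | 1 | 0.27 | 0.63 |
| 0.76 | 7 | 2 | 0.39 | 0.69 |

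In the two middle rows, 15% and 34% of the log effect is lost (1 − ln 0.556/ln 0.50 and 1 − ln 0.635/ln 0.50).

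**5. If rates are lower before allocation.** Let the earlier rate be k times the later usual-care rate. The ratio becomes [fk + (1 − f)RR]/[fk + (1 − f)]. With k = 0.5 (assumed), the outer rows fall from 0.53 to 0.52 and from 0.69 to 0.62.

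**6. Proportions.** Let q be the share of patients who already have the event at allocation. Each arm's whole-stay risk is q + (1 − q)p, so the risk difference shrinks by the factor (1 − q). Take 44.7% in controls (the pressure ulcer rate in the Discussion, used only as an example) against an assumed 20%, two-sided 5%:

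| q | Whole-stay risks | Risk difference (points) | Power, 50 per arm | Power from allocation, 50(1 − q) at risk |
|---|---|---|---|---|
| 0 | 44.7% v 20.0% | 24.7 | 76% | 76% |
| 0.1 | 50.2% v 28.0% | 22.2 | 63% | 71% |
| 0.2 | 55.8% v 36.0% | 19.8 | 51% | 66% |
| 0.3 | 61.3% v 44.0% | 17.3 | 41% | 60% |

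The last column is the fair comparator for an outcome that can occur only once, where patients who already have it leave the risk set.

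**7. Mean total dose.** The expected pre-allocation dose is the same in both arms and cancels from the difference in means. Only the SD grows, by √(1 + r²), where r is the pre-allocation SD over the post-allocation SD (components taken as independent). At 50 per arm and a standardised difference of 0.65, power is 90% for r = 0, then 88%, 83% and 63% for r = 0.25, 0.5 and 1.0.

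**The case against.** The strongest reply is that collecting is not analysing. Complete collection over the stay is what one would want, and counting rules may sit in a full protocol or analysis plan that is not shown. This has force for falls, injuries, catheters and infections. Table 4's entry on pressure ulcer development may already mean new ulcers only, and a monthly falls rate need not be a per-patient whole-stay count. It has less force for antipsychotics, where the article names the quantity to be examined and it is the admission total. Nor does it answer the point that the only window stated for any of these outcomes opens before allocation.

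A reader might infer that whole-stay counting shrinks every GMU effect, or that it touches most of the primary outcomes. The documents do not support either.
- An absolute difference in mean dose or count is not biased under randomisation. A patient sedated before entering GMU has counterparts among the controls.
- Of the primary outcome list, only drug use, falls/injuries and infection have a whole-stay or admission window (antidepressant and benzodiazepine use by reading on from the antipsychotic clause). Restraint and delirium duration have none, and delirium severity, Barthel and satisfaction are not counts over the stay.

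It is also fair to say that the rate illustration leans high. The incident share pairs extremes of general-literature ranges. The equal-rate assumption is doubtful too: the Background links half of geriatric-ward falls to delirium at 15% prevalence, so falls are probably rarer before onset. Where delirium is present on admission and allocation is prompt, the effect is small.

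**Conclusion.** The point holds in a limited form. The stated windows begin at admission, allocation comes later, incident delirium is eligible, and nothing in the text separates earlier events. Followed as written, this attenuates rate ratios, proportions and risk differences and costs precision in mean differences of dose or count.

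The direction follows from the design. The size does not: it rests on an assumed delay to allocation, borrowed incidence ranges, equal stay in both arms and equal event rates before and after allocation. The range of 0.53-0.69 for a true ratio of 0.50 is therefore an illustration, more likely too large than too small under the assumed delays. The change is worth making because it costs little, not because a large bias has been shown.

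**What to change.** **Randomised arms.** State that in-hospital events, catheter days, restraint and drug exposure are analysed from the date and time of allocation to discharge, in both arms alike, and per patient-day at risk where a rate is used. Record catheter, ulcer and drug status at allocation as baseline. Continue to collect the earlier data, which supply that baseline.

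**Pre/post comparison.** Use one time zero that can be defined the same way in all groups, such as the first record of delirium. The pre-implementation cohort relies on available data and has no delirium severity scores (Table 4), so that date may not always be recoverable. Where it is not, label whole-stay results as descriptive.

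**Cost.** A recorded allocation time, slightly fewer counted events, and dated entries for events and drugs. Table 4 already lists daily records for physical restraints. Daily restraint and medication documentation is otherwise described only as part of the GMU programme, so the control arm's forms should be checked for the same dates.

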The primary aim of this study is to compare delirious patients admitted to the Geriatric Monitoring Unit (GMU), compared to usual geriatric care in general ward setting on the following primary measures: (1) Duration of delirium and severity of delirium, (2) Use of physical and chemical restraints, (3) Falls rate, (4) Physical injury rate due to agitated behavior, (5) Functional outcomes/gains in the elderly geriatric patients, (6) Morbidity (such as nosocomial infection rate, urinary catheter use and catheter days, pressure ulcer rate); (7) Patient and family satisfaction score in elderly persons with delirium. We postulate better outcomes in patients admitted to GMU versus usual geriatric care. Our secondary aims include looking at which specific aspects of the interventions would yield the greatest benefit for future translation on a larger scale; the effects of the multicomponent intervention and bright light therapy on sleep of these patients as well as their effect on antipsychotic and sedative-hypnotic use.

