##### Sample size and statistical analyses

We aim to recruit 50 subjects during the pre-implementation and 50 subjects each from the GMU group and control (usual care) group (total 150 study subjects). We based our calculations on a two-sample comparison of means for the GMU and control group using non-repeated measures. Using mean Barthel Index score difference of 10 with standard deviation of 14 with ratio between groups of 1, a sample size of 45 patients in each group will be adequately powered to detect a 10-point mean Barthel Index group differences, with 90% power. Assuming that 10% of patients are lost to follow-up at 1 year, we project a final sample size of 50 (rounded up). Level of significance was set at 5%. Sample size calculation was performed in PS Power and Sample Size Calculations V2.1.30. Statistical analysis will be performed using appropriate statistical methods (univariate and multivariate analyses) for between group comparisons. Appropriate statistical methods will be used for the longitudinal outcome analyses and statistical significance is set at 5%.

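### The stated covariates for the Barthel outcome leave out the admission Barthel score, which is already collected; this gives away precision but causes no bias and no sample-size error

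*Protocol article*

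**What the plan says.** The Data collection section ends with the primary outcomes, and the closing clause gives the adjustment for all of them: "Functional outcomes by way of modified Barthel Index score and (iii) Patient/family satisfaction score; all adjusted for baseline demographics and comorbidities". The modified Barthel Index is among these outcomes.

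Table 4 in the same section shows what the two terms cover. The demographics row reads "Age, race, gender, length of hospital stay". The comorbidity row holds Charlson's index and SIRS. Functional status, as the modified Barthel Index, has its own row, so the admission score falls under neither term.

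The score is collected. The text plans to assess "functional status (using modified Barthel Index) [45] during the initial and pre-discharge phase of patient's admission", and Table 4 marks it for all three groups. For later function it adds: "The functional outcomes in the geriatric patients with delirium include follow-up phone interview at baseline, 6 months and 12 months later".

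The Sample size and statistical analyses section sizes the trial on the Barthel alone: "We based our calculations on a two-sample comparison of means for the GMU and control group using non-repeated measures". It assumes a difference of 10 points, an SD of 14, 90% power and a 5% significance level, giving 45 per group, or 50 after 10% loss. The analysis methods, including the longitudinal ones, are described only as appropriate.

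**The concern.** When an outcome is measured at entry and again later, the entry value is usually a natural first covariate. Here the article names covariates for its primary outcomes and omits the entry value of the one outcome that sets the sample size.

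Two things are at stake. The first is precision: whatever part of follow-up function is predictable from entry function stays in the error term. The second is chance imbalance. With about 45 analysed per group, the groups can differ by a few points in entry function, and without the covariate a share of that difference carries into the estimated effect.

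Both concern the randomised comparison of GMU and concurrent controls. The pre/post comparison is not randomised, so there a difference in admission function would be confounding.

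**Working it through.** **Inputs.** From Sample size and statistical analyses: difference 10, SD 14, ratio 1, power 90%, significance level 5%, 45 per group, 10% loss. Two-sided testing is assumed; a one-sided test needs 34 per group and does not fit the stated 45. The correlation r between entry and follow-up Barthel is not given, so 0.3 to 0.7 is assumed.

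**1. The plan's own figure.** Normal approximation: n = 2(1.960 + 1.282)² × 14²/10² = 41.2, so 42 per group. The t-test needs 42.2, so 43. At 45 per group, power is 91.8% by t-test (92.3% by normal approximation). Loss: 45/(1 − 0.10) = 50. The stated 45 and 50 are sound without any covariate.

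**2. Adding the entry score, if 14 is the SD of the follow-up score.** The residual SD is 14√(1 − r²), so the variance of the group difference is multiplied by 1 − r². The comparison is with no adjustment; n and power use the normal approximation.

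| r | Residual SD | Variance cut | n per group for 90% power | Power at 45 per group | Difference detectable with 90% power at 45 |
|---|---|---|---|---|---|
| 0 | 14.0 | none | 42 | 92.3% | 9.6 |
| 0.3 | 13.4 | 9% | 38 | 94.4% | 9.1 |
| 0.5 | 12.1 | 25% | 31 | 97.5% | 8.3 |
| 0.7 | 10.0 | 49% | 22 | 99.7% | 6.8 |

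Put another way, 45 analysed per group would be worth 45/(1 − r²), or about 49, 60 and 88 per group.

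**3. Gain over the adjustment already planned.** Suppose demographics and comorbidity explain a share R₀ of the variance, and these plus entry Barthel explain R₁. The further cut is 1 − (1 − R₁)/(1 − R₀). With R₀ = 10% (assumed):
- R₁ = 25%: 1 − 0.75/0.90 = 17%
- R₁ = 49%: 1 − 0.51/0.90 = 43%

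With R₀ = 20% these become 6% and 36%. Setting R₁ to 25% or 49% supposes that the planned covariates add nothing once entry Barthel is in the model. The less the two overlap, the closer the gain comes to that in step 2.

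**4. If 14 is instead the SD of change.** With equal variances σ² at both times, the change score has variance 2σ²(1 − r) and the covariate-adjusted score σ²(1 − r²). The ratio is (1 + r)/2: 0.65, 0.75 and 0.85 at r = 0.3, 0.5 and 0.7. Multiplying 42.2 by these gives about 28, 32 and 36 per group. A gain remains, but it now shrinks as r rises.

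**5. Chance imbalance.** If the entry SD is also 14 (assumed), the standard error of the entry difference at 45 per group is 14√(2/45) = 2.95 points. With equal SDs, a share r of an entry difference carries into the unadjusted comparison: at r = 0.5, a 3-point imbalance moves the result by 1.5 points.

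**The case against.** The strongest reply is that the clause is generic. It covers delirium duration, restraints, falls, infections, function and satisfaction together, and it does not say that nothing else may be adjusted for. A condensed article may leave outcome-specific covariates to a fuller plan. The primary aim speaks of "Functional outcomes/gains in the elderly geriatric patients", baseline is listed among the functional time points, and a longitudinal model could use it. Sizing on a simpler method than the one used for analysis is conservative. Barthel scores taken during acute delirium may also predict later function only weakly.

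Much of this stands. The text does not forbid baseline adjustment, and the size of the gain is unknown. It does not remove the point: the article chose to name covariates, and nowhere is entry Barthel among them. If gains means an unadjusted change score, step 4 shows that adjusting for entry score is still more precise at the correlations considered.

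A reader might infer three stronger things that the documents do not support.
- **That the trial is underpowered or the comparison biased without the covariate.** Step 1 shows the stated power is met at 45 per group. Under randomisation, omitting a prognostic covariate leaves the comparison unbiased.
- **That the covariate would make good the power lost to deaths.** The Background cites one-year mortality of 35-40%. At 35%, 50 × 0.65 = 32.5 per group would remain, with 81% power unadjusted and 91% at r = 0.5. But that rate comes from cited literature, the trial excludes dangerously ill and terminal patients, and the rate does not bear on the pre-discharge Barthel. Nor does adjustment among those measured resolve outcomes missing because of death.
- **That the same change should be made at once for AMT and delirium severity.** AMT is not among the listed primary outcomes. DRS is part of daily documentation within the GMU programme, so the first score is not shown to precede GMU care.

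**Conclusion.** The point holds as an inexpensive improvement in efficiency. The named adjustment set omits the entry value of the only outcome used for sizing, although that value is collected. For any material correlation the direction of the gain is clear. Its size depends on two things the document does not give: the correlation, and whether 14 is the SD of the score or of change. The 9% to 49% range is measured against no adjustment. The increment over demographics and comorbidity is smaller where they overlap with entry function, for example 17% to 43% under the 10% assumption in step 3.

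**What to change.** In the sentence that sets the adjustment, add the entry modified Barthel Index as a covariate for the Barthel outcome, alongside demographics and comorbidity. The analysis can be an ANCOVA at a named time point, or a mixed model over discharge, 6 and 12 months with the entry score as covariate.

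State that the entry score is taken before or at allocation. The article places it only in the initial phase of admission, accepts delirium that arises during the stay, and seeks consent after allocation under Zelen's method, so the order is not shown. A score taken after GMU care has begun should not be used as a baseline.

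Extend the change to delirium severity only if the first DRS precedes the start of GMU care.

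The cost is one sentence, with no extra patients. No new data are needed if the initial Barthel is already taken by the time of allocation; otherwise its timing has to be fixed.

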## Background

Delirium is a common and serious condition, which affects many of our older hospitalised patients. The prevalence in hospitalised elderly patients is shown to be as high as 50%, with the diagnosis in 11-24% of older patients upon admission and another 5-35% of them developing delirium during admission [1,2]. It is an indicator of severe underlying illness and requires early diagnosis and prompt treatment. The development of delirium is associated with increased need for nursing surveillance, greater hospital costs and in-hospital mortality rates of 25-33% and one-year mortality rate of 35-40% [3-8]. Complications may also occur related to physical injuries from agitated behaviour, complications of immobility as a result of physical restraints and pharmacologic agents used to control the behaviour in the confused patients and nosocomial infections resulting from the prolonged hospitalization [9]. This in turn translates to increases in length of hospital stay, rates of admission to nursing homes, rates of mortality, and higher healthcare costs.

The importance of delirium is highlighted by its inclusion as a marker for quality of care and patient safety by the National Quality Measures Clearinghouse of the Agency for Healthcare Research and Quality, as higher delirium rates would be expected to correlate with lower quality of hospital care after adjustment for casemix. Moreover, the Assessing Care of Vulnerable Elders Project has ranked delirium among the top 3 conditions for which the quality of care needs to be improved [10,11]. Other worldwide initiatives such as in Western Australia (WA), the Department of Health will be implementing evidenced based Models of Care (including Delirium) across WA Health with other nation-wide efforts made in UK as well.

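### The adjustment set for the primary outcomes omits entry delirium severity for the delirium outcomes and leaves the illness-severity covariate ambiguous

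*Protocol article*

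**What the plan says.** The Data collection section lists the primary outcomes: clinical data that begin with duration and severity of delirium, then functional outcome on the modified Barthel Index, then satisfaction. It ends the list with "all adjusted for baseline demographics and comorbidities". The next sentence names one contrast, "patients with delirium admitted to GMU versus those managed under usual care (control group". Under Study design and patients recruitment, two contrasts are planned: "Our study consist of a pre/post GMU implementation as well as concurrent GMU patients versus patients with delirium managed in the geriatric ward as controls".

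On the candidate covariates, the Data collection text describes "comorbidity and severity of illness data using modified Charlson's comorbidity index [43] and modified severity of Illness index [44". Table 4 has no severity-of-illness entry. Its Comorbidity domain reads "Charlson's index SIRS", marked for all three groups, and SIRS is not expanded anywhere in the article. The Delirium severity domain reads "CAM severity score DRS-98", marked for the GMU group and the concurrent controls but not for the pre-implementation group.

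Sample size and statistical analyses adds only that univariate and multivariate methods will be used, and sizes the study on an unadjusted comparison of mean Barthel scores.

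**The concern.** There are two separate matters.

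- **Entry delirium severity.** A patient's delirium score at entry is a natural predictor of how severe the delirium later is and how long it lasts. The adjustment sentence applies to every listed primary outcome, and neither of its two terms covers that score. The article gives no sample size for the delirium outcomes, so precision on them should not be given away when the score is already on the data list.
- **Illness severity.** The Background says of delirium: "It is an indicator of severe underlying illness and requires early diagnosis and prompt treatment". Acute illness is therefore a plausible prognostic factor, and in the pre/post comparison a plausible confounder. The text and Table 4 label the second instrument differently, and the adjustment sentence does not name it. The covariate could then be settled after the data are seen.

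**Working it through.** **1. The plan's own figure.** Inputs from Sample size and statistical analyses: difference 10 Barthel points, SD 14, ratio 1:1, 5% level (two-sided assumed), 90% power.

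- Normal approximation: n = 2 × (1.960 + 1.282)² × 14² / 10² = 41.2, so 42 per group.
- Two-sample t-test: 42.17, so 43 per group. The stated 45 is within two patients of this.
- Power at 45 per group: 92.3% (normal) or 91.8% (t).
- Loss to follow-up: 45 / (1 − 0.10) = 50, as stated.

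The planned size therefore does not rely on covariate adjustment.

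**2. Is entry delirium severity in the set?** The sentence names demographics and comorbidities. Table 4 keeps Delirium severity as a domain separate from both, so the score is outside the set on any reading.

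**3. Precision given up in the randomised comparison.** Let R² be the extra outcome variance explained by the entry score beyond the planned covariates. The documents give no value, so 0.05 to 0.30 is assumed. The standard error is multiplied by √(1 − R²), whatever the outcome's SD. No SD is given for the delirium outcomes, so the Barthel SD of 14 and 45 per group serve only as a scale: SE = 14 × √(1 − R²) × √(2/45).

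| R² | √(1 − R²) | SE (points) | Power for 10 points | n per group for 90% |
|---|---|---|---|---|
| 0 | 1.000 | 2.95 | 92.3% | 42 |
| 0.05 | 0.975 | 2.88 | 93.5% | 40 |
| 0.10 | 0.949 | 2.80 | 94.7% | 38 |
| 0.20 | 0.894 | 2.64 | 96.6% | 33 |
| 0.30 | 0.837 | 2.47 | 98.2% | 29 |

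The standard error falls by 1 − 0.975 = 2.5%, about 3%, up to 1 − 0.837 = 16%. Equivalently, 50 patients per group would carry the information of 50 / 0.95 = 53 to 50 / 0.70 = 71. The formula suits a continuous score. For delirium duration, which may be skewed or cut short by discharge or death, it is only a guide.

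**4. Illness severity: the two readings.**

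- The text names comorbidity and severity of illness as two constructs with two instruments. Read that way, adjusting for comorbidities leaves severity out.
- The adjustment sentence's two terms match two domain labels in Table 4, and the Comorbidity domain holds SIRS beside Charlson's index. If SIRS is the severity measure, it is inside the set.

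The article does not decide between them.

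**5. Possible size in the pre/post comparison, if severity is omitted.** Bias = r × d × 14, where d is the between-group imbalance in SDs and r the covariate's correlation with outcome. Both are assumed at 0.2 to 0.5 and should be read as what remains after the planned covariates. The low end is 0.2 × 0.2 × 14 = 0.56 Barthel points. The high end is 0.5 × 0.5 × 14 = 3.5 points, against a target difference of 10.

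**The case against.** **The trial does not need this adjustment.** Leaving a prognostic covariate out of a randomised comparison causes no bias, and the Barthel comparison already has about 92% power unadjusted. Both points stand, so this is a matter of efficiency. They do not settle the delirium outcomes, for which no sample size is given.

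**A condensed article leaves model detail to the full protocol or analysis plan.** That is fair, and an unseen plan may name the covariates. But the article does fix a set for all primary outcomes, and the two instrument labels conflict within the article itself.

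**A reader might infer that acute illness severity is definitely left out, or that SIRS is a second, competing index.** Neither is established. Table 4's grouping can place SIRS inside the adjustment, and because SIRS is never expanded it may denote the same instrument.

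**A reader might also infer that the missing delirium score confounds the pre/post contrast.** The adjustment sentence is not the cause: Table 4 shows that delirium severity is not collected before implementation. Calendar-time differences would also remain after any covariate adjustment, and the sentence following the adjustment clause names only GMU versus control.

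**Larger magnitudes can be produced.** At 50 per group the SE is √(2/50) = 0.2 SD, so a bias of 0.3 × 0.4 = 0.12 SD to 0.5 × 0.5 = 0.25 SD raises a nominal 5% error to about 9-24%. Starting from 80% power, an entry score correlated 0.4-0.6 with outcome would be worth 50 / 0.84 = 60 to 50 / 0.64 = 78 patients per arm. These are upper-end illustrations. They treat the analysis as otherwise unadjusted, although demographics and at least the Charlson index are already planned, and the 80% is itself assumed.

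**Conclusion.** The concern holds in a limited form.

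- **Established:** entry delirium severity is outside the stated adjustment for delirium duration and severity, although the instruments are listed for both concurrent groups. The cost is precision, about 3-16% of the standard error under an assumed incremental R² of 0.05-0.30. The Barthel comparison does not fall below its planned power.
- **Established:** the illness-severity instrument carries two labels, and the adjustment sentence does not say whether it is included.
- **Not established:** that illness severity is currently omitted. If it is, the pre/post contrast could be biased by roughly 0.6-3.5 Barthel points under the assumed range. The documents supply neither the imbalance nor the correlation.

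**What to change.** In Data collection, extend the adjustment sentence along these lines: *all adjusted for baseline demographics, comorbidity (modified Charlson index) and illness severity at entry; delirium duration and severity additionally for the DRS-98 severity score at entry, in the GMU versus concurrent control comparison only.* The restriction is needed because the score is not collected in the pre-implementation group.

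Reconcile the modified severity of illness index with SIRS: use one named instrument in the text and in Table 4, scored at entry. State that it is in the adjustment set for both the concurrent and the pre/post comparisons. Table 4 marks SIRS for all three groups, so if that is the instrument, no new data item is needed.

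Two details should be settled in the same edit. Table 4 gives no timing for DRS-98, so confirm that an entry score exists in both concurrent groups and is taken no later than allocation. Also spell out baseline demographics as age, race and gender: the text and Table 4 list length of stay there, and the text also lists delirium duration. Neither is a baseline variable, and the second is a primary outcome.

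The cost is wording and one or two covariates per model. If entry scoring is not already routine in both groups, its timing must also be fixed.
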